### Statistical analyses

We have categorized three study sets: Conventional vs. endoscopic, conventional vs. robotic, and conventional vs. endoscopic and robotic. Additionally, subgroup analyses of a randomized registry trial will be conducted to compare the surgical and oncologic outcomes between the conventional and minimally invasive (endoscopic and robotic) groups. Primary and some secondary outcomes (postoperative complications, the satisfaction of patients and surgeons, and the cost-effectiveness evaluation) and other categorical variables will be examined by the chi-square test or Fisher's exact test. Continuous variables will be examined by t-testing or ANOVA and Mann–Whitney testing or Kruskal–Wallis testing, if needed. The other secondary outcomes (RFS, OS, and cancer incidence rates in 5 years) will be examined using Kaplan–Meier plots and log-rank testing. No imputation will be performed for subjects who have missing data due to dropping out of the study. Data relating to major protocol non-adherence due to patients dropping out of the study will be excluded from the analysis population.

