### Pre-specified subgroup analysis

Because of the long duration and expensive cost of a randomized trial, we will extract random patients from our prospective cohort and conduct subgroup analyses as a randomized registry trial. In a previous study, the rates of grade III complications in the reference group and the robotic group were 34.8% and 17.2%, respectively. For the comparison of complication rates among different surgical methods, the required sample size was calculated as 112 (1:1 random match) according to the method used in a randomized registry trial previously introduced to detect a non-inferiority margin difference, which achieved 80% power between the group proportions of 0.0500. The robotic group proportion is assumed to be 39.8% under the null hypothesis of inferiority. The power was computed for the case in which the actual robotic group proportion is 17.1%. The test statistic used is the one-sided Z test (unpooled). The significance level of the test was targeted at 0.0250. The actual significance level achieved by this design is 0.0265.

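### The 80% power for the 112-patient registry subgroup belongs to a robotic-versus-reference non-inferiority Z test, but the analysis section describes a pooled comparison and assigns complications to chi-square or Fisher's exact test with no margin

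*Protocol article*

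**What the plan says.** Two adjacent sections of the protocol article describe the randomized-registry subgroup.

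**Pre-specified subgroup analysis** gives the calculation:
- Rates come from a previous study: "the rates of grade III complications in the reference group and the robotic group were 34.8% and 17.2%, respectively".
- Size: "the required sample size was calculated as 112 (1:1 random match"), with a margin of 0.05 and 80% power.
- Null: "The robotic group proportion is assumed to be 39.8% under the null hypothesis of inferiority".
- Alternative: "The power was computed for the case in which the actual robotic group proportion is 17.1"%.
- Test: "The test statistic used is the one-sided Z test (unpooled"), at a target level of 0.0250 and an achieved level of 0.0265.

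Only the robotic and reference groups enter this calculation.

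**Statistical analyses** first lists three study sets for the cohort: conventional versus endoscopic, versus robotic, and versus both. It then says that registry-trial subgroup analyses will be done to "compare the surgical and oncologic outcomes between the conventional and minimally invasive (endoscopic and robotic) groups". The next sentence says that primary and some secondary outcomes, with postoperative complications named among them, "will be examined by the chi-square test or Fisher's exact test". The section gives no margin, significance level, sidedness or confidence limit. No endoscopic complication rate appears in the sample size, subgroup or analysis text.

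**The concern.** The two sections differ on two points.

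1. **Who is compared.** The calculation has a robotic arm. The analysis sentence has an arm that pools endoscopic and robotic patients.
2. **What is tested.** The calculation tests whether the robotic rate exceeds the reference rate by 5 points or more. Chi-square and Fisher's exact test ask whether two rates are equal, and neither uses the margin.

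This matters because the 112-patient subgroup is the only comparison in the article with a power statement. The 2000-patient target is said to have been set without statistical calculation. A reader cannot tell which of the two described analyses the 80% refers to. If the choice stays open until the data are seen, the choice of test can decide the conclusion. Someone could also take a non-significant chi-square as support for non-inferiority, although it says nothing about the 5-point margin.

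**Working it through.** **Inputs.** From Pre-specified subgroup analysis: reference rate 0.348; robotic rate 0.171 under the alternative (0.172 where the source study is cited); margin 0.05, since 0.398 − 0.348 = 0.050; one-sided level 0.025; 112 patients 1:1, so 56 per group. Assumed, because the documents do not give them: a two-sided 5% level for chi-square, and any endoscopic rate or share.

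**Step 1. Reproduce the plan's figure.**
- Variance sum: 0.348 × 0.652 + 0.171 × 0.829 = 0.2269 + 0.1418 = 0.3687.
- Distance from the null: (0.348 − 0.171) + 0.05 = 0.227.
- Patients per group: (1.960 + 0.842)² × 0.3687 / 0.227² = 56.2, which agrees with 56 per group to within rounding.
- Exact binomial enumeration of the unpooled Z test at 56 per group gives power 0.800 at 34.8% versus 17.1%, and a level of 0.0265 at 34.8% versus 39.8%. Both match the printed figures, so 112 is the total and the design has been identified correctly. With 17.2% in place of 17.1%, power is 79.6%.

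**Step 2. Same 112 patients and rates, two-sided 5% chi-square, no margin.**
- Mean rate: (0.348 + 0.171)/2 = 0.2595.
- Standard error under equality: √(2 × 0.2595 × 0.7405/56) = 0.0828. Under the alternative: √(0.3687/56) = 0.0811.
- Power: Φ[(0.177 − 1.960 × 0.0828)/0.0811] = Φ(0.18) = 57%. Exact enumeration gives 57.9%.
- The normal formula needs 96 per group (192 in total) for 80%.

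The fall from 80% to 58% comes entirely from dropping the margin: the distance to be detected shrinks from 0.227 to 0.177. Pooling plays no part in it.

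**Step 3. What chi-square can and cannot conclude.** At 56 per group, every outcome in which chi-square is significant in favour of the new arm also meets the 5-point margin. Under the planned rates there is a further 22% probability (80.0% − 57.9%) that non-inferiority is met while chi-square is not significant. For example, 20/56 (35.7%) conventional and 12/56 (21.4%) robotic events give a difference of −14.3 points with a 95% upper limit of +2.2 points. Non-inferiority is met, yet the chi-square p-value is 0.09.

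**Step 4. Effect of pooling, with the non-inferiority test kept.** Pooled rate = (1 − s) × 0.171 + s × (endoscopic rate), where s is the endoscopic share. With s = 0.5:

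| Assumed endoscopic rate | Pooled rate | Non-inferiority power |
|---|---|---|
| 10% | 13.55% | 92% |
| 17.1% | 17.1% | 80% |
| 25% | 21.05% | 62% |
| 34.8% | 25.95% | 37% |

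The direction of the change depends on a rate that the documents do not give.

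**The case against.** The strongest reply is that the subgroup section already names its own test. The chi-square sentence is general: it also covers satisfaction, cost-effectiveness and other categorical variables, and it does not mention the 112 patients. A specific provision can be read as overriding a general one. Conventional versus robotic is also one of the three listed study sets, so that comparison has not been dropped. The study is described as exploratory, and operational detail may sit in documents not shown.

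Much of this stands. It means the article cannot be said to have replaced the Z test, so the 58% is conditional. It does not remove the conflict. The analysis section introduces the registry subgroup, and its next sentence assigns complications to chi-square or Fisher without exempting that subgroup. Even if the Z test governs, the arms still differ: robotic alone in one section, pooled in the other. These are two stated designs that disagree, which is different from detail left out.

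A reader might infer more than the text supports:
- **That power falls to about 50%.** Fisher's exact test does give 49.7% here. But Fisher is usually kept for sparse tables, and the expected event count per group is about 56 × 0.2595 = 14.5, so it would be unlikely to be used.
- **That pooling lowers power.** It does so only if the endoscopic rate exceeds 17.1%. A lower rate raises power, as Step 4 shows.
- **That chi-square can never exclude inferiority.** Step 3 shows that a favourable significant result always does.
- **That the investigators will read non-significance as non-inferiority.** Nothing in the article says so.

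**Conclusion.** The point holds as a conflict between two sections. The 80% power is correct for robotic versus reference under the one-sided unpooled Z test with a 5-point margin, and for that analysis only. It does not describe the pooled, margin-free comparison in the analysis section.

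If a two-sided 5% chi-square were applied to this subgroup at 34.8% versus 17.1%, power would be about 58%, and that would be power for superiority, a stricter claim. This rests on three assumptions: that the chi-square sentence reaches the subgroup, that the level is two-sided 5%, and that the pooled arm has the robotic rate of 17.1%. The effect of pooling itself cannot be sized or signed from the documents. This should be settled before the subgroup is drawn and analysed, but it does not undermine the cohort as a whole.

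**What to change.** In Statistical analyses:
- State that the powered subgroup analysis of grade III or higher complications is robotic versus conventional. Test it for non-inferiority by comparing the upper limit of the two-sided 95% confidence interval for the risk difference (robotic minus conventional) with +5 points.
- Report endoscopic and pooled endoscopic-plus-robotic comparisons in this subgroup as estimates with confidence intervals and no power claim.
- State that a non-significant chi-square result is not evidence of non-inferiority.

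If the pooled chi-square analysis is what is intended, replace the 80% with about 58%, and say that this assumes a two-sided 5% level and an endoscopic rate equal to the robotic 17.1%.

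The cost is wording only, with no extra patients or data. The downside is that the pooled comparison in this subgroup loses its claim to 80% power.

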**Fig. 1 Fig1:**
[figure not shown]
Flowchart of the prospective cohort study

The inclusion criteria for the patients are as follows: adult women older than 19 with breast cancer or a high risk of breast cancer (patients with *BRCA1/2*, *TP53*, *PALB2* mutations, etc.) who are scheduled for a therapeutic or risk reducing mastectomy and want immediate reconstruction. The PI or a physician delegated by the PI provides information about the study and an adequate opportunity to consider all options to all potential trial participants and obtains signed informed consent forms before enrollment. Patients who plan breast-conserving surgery or who are not candidates for IBR will be excluded. The target number of enrolled patients is 2000.

Patients' clinicopathological factors, including height and weight, will be collected, along with data on surgical results, including photographic and oncological results and cost-effectiveness and patient satisfaction data. The basic characteristics, photographs, and satisfaction of patients will be collected preoperatively using the Breast-Q survey. Patient data will be collected within 6 months of surgery, including clinicopathological factors, surgery results (drainage amount, removal date, and complications), postoperative recovery evaluations, complications and adverse reactions, and cost. Between 6 months and 1 year after surgery, the results of surgery, recurrence, a satisfaction survey, intraoperative console video, and postoperative photographs will be collected. Every 12 months thereafter, data on adjuvant therapy (chemotherapy, radiation therapy, targeted therapy, and endocrine therapy), surgical results, recurrence, adverse events, and other unintended effects of the interventions will be investigated and collected until the end of the study period.

Personal information that can identify the subjects will be kept confidential even after the publication of the study. After enrollment, each participant’s name will be encrypted and replaced with a participant number. The datasets collected from each institution will be accumulated and stored in a designated computer on a central server. Access to that database is restricted to authorized researchers.

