#### Secondary endpoints

Recurrence-free survival (RFS) in 5 postoperative years: RFS events include locoregional recurrence, distant recurrence, and death by any cause. Contralateral breast cancer and a second primary malignancy are considered to be censored data.

Cancer incidence rate in 5 postoperative years: Cancer incidence rate for those who underwent a prophylactic mastectomy.

Patient satisfaction with reconstruction results preoperative (baseline) and 6 to 12 postoperative months: Reconstruction module with pre- and postoperative scales for satisfaction with the abdomen, as assessed by BREAST-Q version 2.0. (This scale should be completed only by patients who have had reconstruction using a TRAM flap or DIEP flap. Otherwise, it is skipped.) Satisfaction with the back, as assessed by BREAST-Q version 2.0. (This scale should only be completed by patients who have had reconstruction using an LD flap. Otherwise, it is skipped.) Satisfaction with implants, as assessed by BREAST-Q version 2.0. (This scale should only be completed by patients who have had reconstruction using implants. Otherwise, it is skipped.) In all scales, higher scores reflect better outcomes.

Surgeon's satisfaction with surgery within 6 postoperative months: Assessed using scoring criteria for cosmetic assessment [52], response options (overall symmetry, postoperative scar, NAC symmetry, etc.), and range (0–10). Higher scores reflect better outcomes.

Evaluation of the cost-effectiveness of the definitive surgery according to the surgical method: Assessed by conducting a patient’s survey 6 months to 1 year after the last surgery. This evaluation uses the EuroQol five-dimension scale, Korean version questionnaire. In all scales, higher scores reflect better outcomes.

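### Patient satisfaction, surgeon satisfaction and cost-effectiveness are assigned to chi-square or Fisher tests, although the protocol defines them as scores with no cut-off

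*Protocol article*

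**What the plan says.** The Statistical analyses section assigns tests by outcome type. Primary and some secondary outcomes are listed in a parenthesis and given one pair of tests, with Fisher's test as the alternative: "postoperative complications, the satisfaction of patients and surgeons, and the cost-effectiveness evaluation) and other categorical variables will be examined by the chi-square test". A separate sentence follows and names no endpoint: "Continuous variables will be examined by t-testing or ANOVA and Mann–Whitney testing or Kruskal–Wallis testing, if needed".

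The Secondary endpoints section defines the three outcomes as follows.

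- **Patient satisfaction:** "Patient satisfaction with reconstruction results preoperative (baseline) and 6 to 12 postoperative months", measured by BREAST-Q version 2.0 scales for abdomen, back and implants. Each scale is limited to one type of reconstruction; for implants, "This scale should only be completed by patients who have had reconstruction using implants". The scoring direction is given as "In all scales, higher scores reflect better outcomes".
- **Surgeon satisfaction:** a cosmetic assessment with "response options (overall symmetry, postoperative scar, NAC symmetry, etc.), and range (0–10). Higher scores reflect better outcomes".
- **Cost-effectiveness:** "This evaluation uses the EuroQol five-dimension scale, Korean version questionnaire", completed 6 months to 1 year after the last surgery, again with higher scores better.

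No cut-off, responder definition or set of categories is given for any of the three. The Methods/Design section adds that "satisfaction of patients will be collected preoperatively using the Breast-Q survey" and that cost is among the data collected within 6 months of surgery.

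**The concern.** The two sections disagree on what kind of variable these outcomes are. One defines scores on which more is better. The other calls them categorical and sends them to a contingency-table test.

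Three things follow if the analysis is run as written. A chi-square test on the uncut score treats its values as unordered labels and spreads the signal over many degrees of freedom. Cutting the score first loses information and, with no cut fixed in advance, leaves the choice open until the data have been seen. For cost-effectiveness, the test gives only a p-value for association; it does not produce a cost difference, an effect difference or a relation between them. The Discussion presents large-scale patient-reported data as an advantage of this study, so the analysis of those data should be fit for the purpose.

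**Working it through.** **Step 1: outcome type against assigned test.**

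| Outcome | Definition (Secondary endpoints) | Cut-off given | Test (Statistical analyses) |
|---|---|---|---|
| Patient satisfaction | BREAST-Q 2.0 scales, higher is better | none | chi-square or Fisher |
| Surgeon satisfaction | score 0 to 10, higher is better | none | chi-square or Fisher |
| Cost-effectiveness | EQ-5D, higher is better | none | chi-square or Fisher |

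The sentence on continuous variables does not resolve this. It names no endpoint, whereas the three outcomes are named in the categorical sentence, where the word for the remaining variables (other) places them in the same class.

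**Step 2: inputs for a size.** The documents give no standard deviation, target difference, cut-off or power for these endpoints, and the overall sample size was set without a statistical calculation. There is therefore no plan figure to reproduce. Assumptions for illustration: normally distributed scores, two equal arms, two-sided alpha 0.05, 80% power for the score analysis.

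**Step 3: information kept after a cut.** For a cut at quantile q with normal deviate c, relative efficiency = φ(c)² / [q(1 − q)], and the sample size inflation is its inverse.

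- Median: φ(0)² / 0.25 = (1/2π) / 0.25 = 2/π = 0.637; inflation 1.57.
- 80th percentile: 0.490; inflation 2.04.
- 90th percentile: 0.342; inflation 2.92.

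**Step 4: the same in patients and power.** Score analysis: n per arm = 2(1.960 + 0.842)² / d², where d is the standardised difference. Cut analysis: two proportions, 0.5 against Φ(d), with the cut at the control median.

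| d | n per arm, score | n per arm, median split | Power of the split at the score n |
|---|---|---|---|
| 0.2 | 393 | 620 | 61% |
| 0.3 | 175 | 278 | 60% |
| 0.5 | 63 | 102 | 59% |

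**Step 5: chi-square without a cut.** With k unordered categories in two groups the test has k − 1 degrees of freedom. Suppose the whole signal lies in the ordered trend, so that the noncentrality stays at (1.960 + 0.842)² = 7.85. Power is then 80% at 1 degree of freedom, 60% with 5 categories and 43% with 11, the number of whole-number values on a 0 to 10 score.

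**Step 6: cost-effectiveness.** A cost-effectiveness result needs a cost difference and an effect difference, considered together. Cost is collected (Methods/Design) and EQ-5D is collected (Secondary endpoints). The assigned test uses at most one of them at a time.

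**Step 7: baseline, where it exists.** Adjusting for the same scale measured before surgery leaves a fraction 1 − r² of the variance: 0.91, 0.75 and 0.51 at assumed correlations r of 0.3, 0.5 and 0.7.

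**The case against.** The strongest reply is that suitable tests are already in the plan. The next sentence offers t-tests, ANOVA and rank tests, so the three outcomes may simply have been listed in the wrong sentence of a condensed article. That makes the repair easy, but the text as published still names the wrong tests, and a fuller plan would have to contradict it rather than fill a gap. It may also be said that EQ-5D item levels are ordered categories that could be cross-tabulated. That is true of the items, but the article treats the instrument as a score, and cross-tabulation still gives no cost-effectiveness result.

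The objection on weight stands. These are secondary endpoints in a study that calls itself exploratory, and the only power calculation in the article concerns complication rates in the matched subgroup. The percentages above depend on normality and on where a cut would fall, neither of which the plan specifies.

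A reader might infer more than the documents support:

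- **That baseline BREAST-Q will go unused.** No named test uses it, but the article only lists tests and does not rule out adjustment or change scores. Baseline is part of the endpoint title, and a condensed article commonly leaves such detail to the analysis plan.
- **That the abdomen, back and implant scales will be pooled.** No passage proposes this; each scale is confined to its own reconstruction type.
- **That one BREAST-Q scale common to all women could carry a baseline-adjusted main analysis.** The article names no such scale, and the Abstract describes the baseline as expectations and the follow-up as results, which may be different constructs.
- **That a bias from baseline imbalance can be put in points.** Neither the imbalance nor the slope is in the documents, so any such figure would be invented.

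**Conclusion.** The mismatch is real and lies in the text: three outcomes defined as scores are named for tests of categorical data, with no categories defined. Under the stated assumptions, a median split keeps about 64% of the information and lowers 80% power to about 60%. More extreme cuts cost more, up to about 2.9 times the patients at the 90th percentile. For cost-effectiveness the problem does not depend on any assumption, because the assigned test cannot deliver the result. The point is worth correcting but limited in reach: the primary endpoints and the one stated power calculation are untouched. Baseline adjustment belongs in the remedy as a sensible step for groups that are not randomised, not as a demonstrated fault in the plan.

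**What to change.** In the Statistical analyses section, remove patient satisfaction, surgeon satisfaction and cost-effectiveness from the chi-square and Fisher list, and state instead:

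- **BREAST-Q:** compare each scale as a score, within the reconstruction type that completes it, by t-test or ANOVA, rank test or the regression equivalent, and report a mean difference with a confidence interval. Where the same scale is collected before and after surgery, adjust for its baseline value. Satisfaction with implants can hardly have a meaningful value before an implant is placed, so this will not apply to every scale.
- **Surgeon score:** compare as a 0 to 10 score in the same way.
- **Cost-effectiveness:** report EQ-5D as a score and cost as a between-group difference with a bootstrap confidence interval, and relate the two as incremental cost against EQ-5D difference. Note as a limitation that the article describes EQ-5D only after surgery, so a preoperative difference between groups cannot be removed from it.

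The cost is a change of wording and a little more analysis work. Preoperative BREAST-Q and cost are already being collected, and nothing in enrolment or follow-up changes.

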## Discussion

This study will provide evidence about the surgical outcomes, oncologic outcomes, and patient satisfaction with RNSM and ENSM, compared with CM.

This prospective cohort study has some advantages over previous retrospective studies conducted in a single center or with a single surgeon. The sample size of the study is larger than previously published studies of RNSM. Additionally, our protocol will collect large-scale PRO data about cosmesis after RNSM. The participation of many surgeons from multiple institutions will allow us to observe the effects of different surgeons or institutions on the clinical outcomes of the surgical procedures. In Korea, an increasing number of breast surgeons has been performing RNSM because of active educational programs and systematic research activities. Therefore, the involvement of many skilled surgeons will produce accurate clinical outcomes for the procedures. However, because this is not a randomized controlled trial, selection bias might still occur in determining the surgical modality for each subject. To overcome that limitation and secure the surgical and oncologic outcomes from a new, innovative surgical procedure, we are planning a randomized controlled trial for the near future.

Through this study, we wish to confirm that minimally invasive breast surgery can be considered as a standard treatment for women with breast cancer and as a preventive treatment for women with a high risk of pathogenic variants.

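### The only tests named for comparing self-selected surgical groups are unadjusted, so differences in case mix, surgeon and institution stay mixed with the effect of the surgical method

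*Protocol article*

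**What the plan says.** The section Statistical analyses sets up the comparisons: "We have categorized three study sets: Conventional vs. endoscopic, conventional vs. robotic, and conventional vs. endoscopic and robotic". It then assigns a test to each type of outcome:

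- The complication endpoints (primary), some secondary outcomes and "other categorical variables will be examined by the chi-square test", or by Fisher's exact test.
- "Continuous variables will be examined by t-testing or ANOVA", with rank tests where needed.
- "The other secondary outcomes (RFS, OS, and cancer incidence rates in 5 years) will be examined using" Kaplan–Meier plots and the log-rank test.

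The Discussion acknowledges that "because this is not a randomized controlled trial, selection bias might still occur in determining the surgical modality for each subject". It also presents multicentre participation as an opportunity to "observe the effects of different surgeons or institutions on the clinical outcomes of the surgical procedures". The remedy it offers for selection bias is a separate randomised trial in the future.

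The Pre-specified subgroup analysis draws patients at random from the cohort in a 1:1 random match, 112 in total. It names no matching variables.

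**The concern.** None of the named tests adjusts for anything, and the article itself gives reasons to expect the groups to differ before surgery:

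- **Selection of patients.** The Background says robotic surgery has gone to selected patients and BRCA1/2 carriers, and that endoscopic surgery is laborious in large and ptotic breasts.
- **Different operations.** The conventional arm takes total, skin-sparing and nipple-sparing mastectomy through any incision. The other two arms are defined as nipple-sparing procedures.
- **Mixed indication.** Therapeutic and risk-reducing patients enter the same comparison.
- **Surgeon and institution.** The Discussion expects both to affect outcomes, but no stated analysis contains either.

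An unadjusted p-value then answers whether the groups differ, not whether the operation makes the difference. The Discussion hopes to confirm minimally invasive surgery as a standard treatment, and that needs the second answer.

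**Working it through.** **1. The plan's own figure.** The 2000-patient cohort was sized without a statistical calculation, so there is nothing to reproduce there. The subgroup figure of 112 can be checked. Inputs from Pre-specified subgroup analysis: reference rate 0.348, robotic rate 0.171 under the alternative, margin 0.05, one-sided alpha 0.025, power 80%, unpooled Z test.

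- Distance to the margin: 0.05 + 0.348 − 0.171 = 0.227.
- Variance term: 0.348 × 0.652 + 0.171 × 0.829 = 0.2269 + 0.1418 = 0.3687.
- n per group = (1.960 + 0.842)² × 0.3687 / 0.227² ≈ 56.2, rounded up to 57 (114 in total).
- Exact binomial enumeration at 56 per group gives power 0.8004 and actual alpha 0.0265, which matches the article's 112, 80% and 0.0265.

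The arithmetic is sound. It treats the two groups as comparable apart from the surgical method.

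**2. What random extraction does.** Let a risk factor have prevalence q_C in conventional patients and q_R in robotic patients. A random sample from each group has expected prevalences q_C and q_R again. Sampling therefore keeps the expected imbalance and only reduces the sample size. Only matching on named variables, or actual randomisation of surgery, would remove it.

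**3. Hypothetical size.** The article gives no case mix by group, so the inputs here are assumptions. Take no true effect of method, one binary factor with risk ratio RR, and base risk b in patients without it. The expected rate in a group with prevalence q is b(1 − q) + b·RR·q.

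*Milder case: b = 0.20, RR = 1.5, prevalence 40% vs 20%.*

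- Conventional: 0.20 × 0.60 + 0.30 × 0.40 = 0.240.
- Robotic: 0.20 × 0.80 + 0.30 × 0.20 = 0.220.
- Spurious difference: 2.0 points. Standard error at 1000 per group: √[(0.240 × 0.760 + 0.220 × 0.780)/1000] = 0.0188.
- Ratio 1.06; a two-sided 5% test rejects in about 19% of studies.

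*Stronger case: b = 0.15, RR = 2, prevalence 45% vs 20%.*

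- Conventional: 0.15 × 0.55 + 0.30 × 0.45 = 0.2175.
- Robotic: 0.15 × 0.80 + 0.30 × 0.20 = 0.180.
- Spurious difference: 3.75 points. Standard error at 1000 per group: 0.0178.
- Ratio 2.10; rejection in about 56% of studies.

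With a 1400/600 split the rejection rates are about 16% (milder) and 48% (stronger) for the pooled chi-square test; an unpooled Z test gives about 50% in the stronger case. In the milder case with only a 10-point imbalance (30% vs 20%), the difference is 1 point and rejection at 1000 per group is about 8%. The nominal rate is 5% throughout.

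**The case against.** The best defence is that this is an article condensing a longer protocol. Covariate lists and propensity models are often left to the full protocol or the analysis plan, and nothing in the article rules out adjustment. The study also calls itself exploratory and discloses selection bias openly.

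Part of this stands. The absence of a covariate list would be no finding. But the article is not silent on method: it assigns a test to the primary and survival outcomes, and every one is unadjusted. A later plan that adjusted would have to replace or add to what is stated here. Neither the exploratory label nor a future trial repairs the comparisons in this study.

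Some narrower objections are right. Cancer incidence is restricted to women having prophylactic surgery, so indication mix does not confound that log-rank test. The subgroup's random match follows a cited method that is not shown, so matching on covariates cannot be excluded, although none is named.

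A reader might also infer that ignoring surgeon clustering makes the standard errors too small. The document does not support this. It depends on how methods are spread over surgeons. If each surgeon favours one method, the errors are too small; if surgeons perform both, they may be too large. Participating surgeons must have had robotic training and conventional surgery is an arm of the same study, so crossing is plausible, and the split is not given.

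**Conclusion.** The point holds: the stated analyses of both complication endpoints and of the survival outcomes compare non-randomised groups without adjustment, and the surgeon and institution effects promised in the Discussion have no analysis behind them. This should be corrected before the comparisons are run, because it decides whether the primary result can be interpreted.

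The figures of 2 to 3.75 points and 19% to 56% rejection are hypothetical and rest wholly on assumed prevalences and risk ratios. The true size and direction of the bias cannot be derived from the document.

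Three stronger readings are not supported:

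- That the authors claim group differences as effects of the method. They acknowledge selection bias; the confounding is a consequence of the tests they name.
- That the bias can be judged against the 5-point non-inferiority margin. That margin belongs to the 112-patient subgroup; the cohort tests have none.
- That every covariate needed is known to be recorded. No case report form is shown. The article names height, weight and clinicopathological factors in general terms, does not list stage as a collected item and never mentions neoadjuvant therapy.

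**What to change.** - **Complication endpoints.** Make the main comparison a propensity-score-weighted or regression-standardised risk difference with a confidence interval, for both endpoints.
- **Recurrence-free survival.** Use a covariate-adjusted or weighted Cox model.
- **Covariates.** Pre-specify pre-operative variables: age, body mass index from height and weight, therapeutic or risk-reducing indication, institution, calendar year, and other pre-operative clinicopathological factors such as stage where recorded.
- **Surgeon and institution.** Account for them by a random effect or clustered standard errors, and report the variation that the Discussion promises.
- **Subgroup.** Match on named covariates instead of at random.
- **Named tests.** Keep chi-square, Fisher and log-rank as descriptive results.

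Weighting cannot balance operations that have no counterpart in the other arm, so the plan should also state which conventional operations form the comparator.

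The cost is additional text in the analysis plan, more analysis work, slightly wider intervals and agreement on the covariate set before the data are compared. Recruitment and treatment are unaffected. Whether any data item must be added depends on what the case report form already records.
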